## Abstract

**Background:**

Sarcopenia is a progressive and generalised loss of muscle mass and function with advancing age and is a major contributor to frailty. These conditions lead to functional disability, loss of independence, and lower quality of life. Sedentary behaviour is adversely associated with sarcopenia and frailty. Reducing and breaking up sitting should thus be explored as an intervention target for their management. The primary aim of this study, therefore, is to examine the feasibility, safety, and acceptability of conducting a randomised controlled trial (RCT) that evaluates a remotely delivered intervention to improve sarcopenia and independent living via reducing and breaking up sitting in frail older adults.

**Methods:**

This mixed-methods randomised controlled feasibility trial will recruit 60 community-dwelling older adults aged ≥ 65 years with very mild or mild frailty. After baseline measures, participants will be randomised to receive the Frail-LESS (LEss Sitting and Sarcopenia in Frail older adults) intervention or serve as controls (usual care) for 6 months. Frail-LESS is a remotely delivered intervention comprising of tailored feedback on sitting, information on the health risks of excess sitting, supported goal setting and action planning, a wearable device that tracks inactive time and provides alerts to move, health coaching, and peer support. Feasibility will be assessed in terms of recruitment, retention and data completion rates. A process evaluation will assess intervention acceptability, safety, and fidelity of the trial. The following measures will be taken at baseline, 3 months, and 6 months: sitting, standing, and stepping using a thigh-worn activPAL4 device, sarcopenia (via hand grip strength, muscle mass, and physical function), mood, wellbeing, and quality of life.

**Discussion:**

This study will determine the feasibility, safety, and acceptability of evaluating a remote intervention to reduce and break up sitting to support improvements in sarcopenia and independent living in frail older adults. A future definitive RCT to determine intervention effectiveness will be informed by the study findings.

**Trial registration:**

ISRCTN, ISRCTN17158017; Registered 6 August 2021, https://www.isrctn.com/ISRCTN17158017

**Supplementary Information:**

The online version contains supplementary material available at 10.1186/s40814-022-01225-7.

## Introduction

Sarcopenia is a progressive and generalised loss of muscle mass and muscle function with advancing age [1]. In community-dwelling older men and women in the UK with a mean age of 67 years, the prevalence of sarcopenia was 4.6% and 7.9%, respectively [2]. A systematic review of adults aged ≥ 50 years, though, reported that the prevalence of sarcopenia in this population group could be as high as 29% [3]. This condition is associated with a range of health problems such as functional disability, falls, unplanned hospital admissions, poor quality of life, osteoporosis, cardiovascular disease, and premature mortality [4]. There is also a rapid rate of decline in activities of daily living (ADL) with 19–39% of community-dwelling older adults with sarcopenia becoming dependent on others for ADL over a 2-year period [5]. Sarcopenia is considered one of the main contributors to the development of frailty and is a key mediator in the pathway through which negative health outcomes of frailty arise [6]. Frailty can be defined as a clinical state in which an individual’s vulnerability for developing increased dependency and/or mortality when exposed to a stressor is increased [7]. This syndrome has multiple causes characterised by diminished strength, endurance, and physiological function that increases vulnerability to co-morbidities, dependency on others for ADLs, and death [7]. The risk of all-cause mortality, unplanned hospitalisation and nursing home admission over a 1-year period is increased by 92%, 93%, and 89%, respectively, in individuals with mild frailty [8]. Moderate and severe levels of frailty are associated with markedly higher risk of these outcomes [8]. It is thus important to develop interventions to reduce the progression of sarcopenia and frailty in older adults to support maintenance of independent living and reduce the risk of adverse health outcomes.

Reducing sedentary behaviour (i.e. any waking behaviour with an energy expenditure ≤ 1.5 METs while sitting, lying or reclined [9]) may be an appropriate initial intervention target for the prevention and management of sarcopenia and frailty. At this initial stage, sedentary time could be replaced and broken up with standing or light-intensity physical activity. This may set the foundations for progressing onto moderate-to-vigorous intensity physical activity, which is unlikely to be achievable to begin with for individuals with chronic disease or physical impairments [10]. A focus on reducing sedentary behaviour is supported by evidence that increased daily sitting time is negatively associated with muscle mass and physical function [11, 12] with each additional hour of daily sitting increasing the risk of sarcopenia by 33% in community-dwelling older adults [13]. Time spent engaging in sedentary behaviour was likewise associated with higher frailty and explained a greater proportion of variance in this outcome than time spent in moderate-to-vigorous physical activity [14].

In addition to total sedentary time, the manner in which sedentary time is accumulated also appears to be important for optimising health in older adults. A higher number of breaks in sitting (i.e. moving from sitting to standing or walking) is related to improved physical function, reduced difficulty in ADL, reduced frailty and a 45% reduced risk of sarcopenia [12, 15–17]. These health risks were independent of moderate-to-vigorous-intensity physical activity levels [15, 16], meaning that reducing and breaking up sitting with standing or light-intensity physical activity could be important intervention targets. Indeed, reducing and breaking up sitting is recommended in national and international physical activity guidelines for older adults and is particularly encouraged for frail older adults for whom more strenuous activities are less feasible [18, 19]. Interventions are thus needed to support reducing and breaking up sitting to improve sarcopenia, slow the progression of frailty and to maintain independent living.

The general older adult population spend 9.4 h a day being sedentary according to a systematic review of 350,000 participants, making them the most sedentary age group [20]. As older adults have the highest prevalence of chronic disease and consider interventions targeting sedentary behaviour to be more acceptable than structured exercise approaches due to barriers such as pain, fatigue, and risk of injury [21, 22], investigating the feasibility and efficacy of interventions to reduce sedentary time in community-dwelling older adults is warranted. An 8-week intervention consisting of motivational interviewing, goal setting, self-monitoring diaries, and mailed feedback (on sitting, standing, stepping, and sit-to-stand transitions at 1 and 3 weeks) significantly reduced sitting by 27 min per day in older adults who were overweight or obese [23]. Sitting time in this intervention was primarily replaced by standing, which increased by 25 min per  day [23]. A systematic review of seven randomised controlled trials (RCTs) in community-dwelling older adults found a mean reduction of 45 min per day in total sedentary time for sedentary behaviour interventions compared with controls, albeit there was insufficient data to pool the effects on breaks in sedentary time [24]. Due to limited evidence and small sample sizes, there was also uncertainty regarding the effectiveness of these interventions for improving physical and mental health, including physical function [24].

It remains unknown whether the intervention findings in older adults are generalisable to individuals living with frailty who have difficulty with ADLs and engage in significantly higher volumes of sedentary time [14]. An intervention in community-dwelling older adults with frailty (*n* = 23) that comprised of face-to-face motivational interviewing, physical function test feedback, plus visual and real-time feedback on sitting using a wearable device, reported significant improvements in breaks in sedentary time, physical function (timed up and go and sit-to-stand tests), and quality of life after 14 weeks [25]. There was, however, no change in daily sitting, which could be expected given this study was not powered to detect a change in this outcome [25]. This pilot study was also limited as it did not include a usual care control group and had a high dropout rate of 45% [25]. However, a powered RCT (*n* = 43) in older adults with frailty did report a 30 ± 10 min/day reduction in sedentary time after a 16-week intervention consisting of home-based standing exercises, face-to-face health education, and telephone support [26]. Nevertheless, there was no change in the number of breaks in sedentary time, and standing time or physical activity were not reported so it is unclear what activities sedentary time was replaced with. Furthermore, intervention effects on health and wellbeing outcomes were not evaluated [26].

Overall, the literature regarding interventions focusing on reductions in sedentary time in community-dwelling older adults is scarce and characterised by studies that are short-term (typically < 3 months), low quality, predominantly conducted with healthy participants and have lacked evaluation of health outcomes relevant to older adults, including sarcopenia-related outcomes [24, 27]. Investigating the feasibility, safety, and acceptability of an intervention to improve sarcopenia and independent living in older adults with frailty via reducing and breaking up sitting is therefore warranted. Furthermore, an intervention that is delivered remotely and is suitable for individuals who may be experiencing physical or social isolation (representing 7–17% of the older population [28]), or physical distancing due to location or for infectious disease control, has not been evaluated. This is particularly relevant for individuals with frailty who may have difficulty in getting outside of the home independently or are particularly concerned about minimising contact with people outside of their household, leading to increased sedentariness [29, 30]. The primary aim of this study is to examine the feasibility, safety, and acceptability of conducting a definitive RCT to evaluate a remotely delivered intervention to improve sarcopenia and independent living through reducing and breaking up sitting in frail older adults.

The main objectives are to:Determine an appropriate participant recruitment strategy;Evaluate participant retention and data completion rates for the primary outcome in a future definitive RCT;Assess acceptability of randomisation to study groups;Evaluate intervention acceptability, fidelity, and adherence;Determine trial safety.

The secondary objectives are to explore the potential efficacy of the intervention for improving sarcopenia, physical function, device-assessed daily sitting, prolonged sitting, breaks from sitting, standing and stepping, mood, wellbeing and quality of life**.**

## Methods

### Study design

This is a randomised controlled feasibility trial that will be conducted and reported following the Consolidation Standards of Reporting Trials statement for pilot and feasibility trials [31]. The reporting of the study protocol follows the Standard Protocol Items: Recommendations for Interventional Trials statement [32]. After baseline measures, participants will be randomised to the intervention (Frail-LESS) or control (continue with usual healthcare) groups. Measurements will then be repeated 3 months and 6 months after group allocation. This intervention duration and the timing of measurements was deemed appropriate for determining the feasibility of the study and intervention acceptability. A flow diagram providing an overview of the study can be seen in Fig. 1.

**Fig. 1 Fig1:**
[figure not shown]
Study flow diagram

### Study setting

This study will be conducted with community-dwelling older adults living in the London metropolitan area, England. Study measurements will be taken at Brunel University London or at participants’ homes depending on participant preference and ability to travel to the University campus. All components of the intervention will be delivered remotely.

### Participant recruitment

The recruitment strategy for the study will include GP practices sending out SMS text messages to potentially eligible patients in their databases. Database searches will be based on patient age, community-dwelling, and a classification of mild or moderate frailty according to an electronic frailty index (eFI) score of 0.13–0.24 and 0.25–0.36, respectively [8]. Database searches will include patients classified with moderate frailty by the eFI as they may be eligible for the present study according to the Clinical Frailty Scale eligibility criteria explained below [33]. The North West London Local Clinical Research Network will support recruitment from GP practices. Participants will also be recruited through Lindus Health, which is a registered UK company that provides recruitment services to health research and clinical trials. Lindus Health use paid advertising on social media (Facebook; Meta, CA, USA), which will be targeted at the North West London region. Email circulation to Brunel Older People’s Reference Group and a study webpage will also be used for recruitment. Potentially eligible participants will be asked to express their interest by email, phone, click-throughs on social media posts, or scanning a Quick Response code provided on recruitment materials. A researcher will then contact interested individuals by email and telephone to carry out screening. 

### Participant eligibility criteria

Screening for participant eligibility will be administered over the phone by a researcher with a clinical health professions background. Eligible participants for this study will be community-dwelling older adults aged ≥ 65 years living with very mild or mild frailty classified according to the Clinical Frailty Scale version 2.0 [33]. Very mild frailty describes people who are not dependent on others for daily help, but often have symptoms that limit activities; a common complaint is being “slowed up” and/or being tired during the day. Mild frailty describes people who have more evident slowing and need help in high order instrumental activities of daily living. Typically, mild frailty progressively impairs shopping and walking outside alone, meal preparation, and housework. Additional inclusion criteria are (1) participants spend the majority (> 60%) of the waking day sitting, measured via self-report using the International Physical Activity Questionnaire item (“During the last 7 days, how much time did you spend sitting on a week day?”) and (2) have a Functional Ambulation Category rating of ≥ 4, i.e. able to ambulate independently with or without a walking aid on level surfaces without supervision or assistance from another person [34].

Exclusion criteria include being unable to communicate in English to a level needed for effective engagement in the study, any physical or mental impairment affecting participants’ ability to stand and walk, and cognitive impairment (score ≥ 7 in the Six-Item Cognitive Impairment Test [35]).

Individuals who are identified as being eligible will be invited to provide written informed consent and to make an appointment to have baseline measures taken.

### Sample size

The target sample size is 40 participants (*n* = 20 in each the intervention and control groups), which is in line with sample size recommendations for pilot and feasibility studies [36, 37]. This number of participants is, therefore, sufficient for addressing the primary objectives of the study relating to feasibility, safety, and acceptability. To allow for 30% attrition, the study aims to recruit 60 participants.

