### Randomisation

Randomisation will be undertaken using an online tool (www.randomizer.org) with a fixed block size of four to allocate participants on an individual basis at a ratio of 1:1 to the intervention (Frail-LESS) and control (continue with usual healthcare) groups. This approach will be used to increase the likelihood of balanced numbers in the trial arms. The randomisation will be conducted by a researcher independent from the study team. Researchers and participants will be blinded to group allocation until baseline measurements have been completed.

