### Data analysis

Feasibility analysis will include calculating rates for participant eligibility (number eligible/number assessed for eligibility × 100), recruitment (number randomised/number eligible × 100), retention (number who complete measurements at 3 and 6 months/number enrolled into study × 100), and missing data (number of complete datasets for outcome measures/number of participants enrolled × 100). To assess trial safety, frequency of falls, hospital admissions and adverse events will be calculated for each group in addition to exploring trends in pain and fatigue (using mean ± SD).

All interviews will be transcribed verbatim using the automated transcription feature of Microsoft Teams (Microsoft Corporation, WA, USA) or a transcribing software (Otter.ai; CA, USA) for interviews conducted by other means, e.g. phone call. Transcripts will be subsequently checked for accuracy by the research team. The Framework Method [77] will be used to analyse this data. This will include deductive and inductive coding to generate themes related to positive and negative participant experiences in relation to intervention acceptability, the intervention’s active ingredients, appropriateness of data collection procedures and factors affecting implementation of the trial. Quotes will be used to illustrate these themes. Deductive coding will be used to evaluate the intervention in the context of the theoretical framework for acceptability of healthcare interventions [75]. This framework explores acceptability in the context of affective attitude, burden, ethicality, intervention coherence, opportunity costs, perceived effectiveness, and self-efficacy. Inductive coding will allow for data-driven insights and contextual factors to be explored. Intervention fidelity will be explored in terms of participant and health coach adherence and engagement with the intervention in relation to the planned protocol. Rating scales within the process evaluation questionnaires will be descriptively analysed based on means, SD, and frequencies.

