### Progression criteria to a definitive trial

Progression from this feasibility trial to a definitive full RCT will be based on the following criteria:The required number of participants are recruited in the intended timeframe.At least 70% of the participants complete the study and provide valid primary outcome data (sarcopenia) at all time points.The intervention is deemed to be acceptable and safe to the participants.The intervention is delivered as planned.

In the case that these criteria are not met, factors affecting implementation of the trial will be explored to identify potential issues that can be adapted in preparation for a full trial.

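### The protocol calls 20 per arm sufficient for safety on general pilot-study guidance alone, and lets the intervention be judged safe from raw frequencies and means with no measure of uncertainty

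*Protocol article*

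**What the plan says.** Safety is one of the main objectives listed at the end of the Introduction: "Determine trial safety".

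The Sample size section sets the number: "The target sample size is 40 participants (*n* = 20 in each the intervention and control groups"). Its justification is that this is a number "which is in line with sample size recommendations for pilot and feasibility studies [36, 37"]. From that alone it concludes: "This number of participants is, therefore, sufficient for addressing the primary objectives of the study relating to feasibility, safety, and acceptability". It then adds: "To allow for 30% attrition, the study aims to recruit 60 participants". Allocation is 1:1 (Randomisation), so up to 30 per arm may be exposed.

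The safety analysis is in Data analysis: "To assess trial safety, frequency of falls, hospital admissions and adverse events will be calculated for each group". Pain and fatigue are handled by looking at trends in means with standard deviations.

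Safety returns in Progression criteria to a definitive trial as a condition for going on: "The intervention is deemed to be acceptable and safe to the participants". The completion criterion in the same list has a number (70%); the safety criterion has none. Under Trial monitoring, a Trial Steering Committee with an independent chair watches over participant safety, and there is no data monitoring committee.

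**The concern.** The sufficiency sentence is a positive claim in the text. It is not a gap that an unseen analysis plan could fill. A plan could add intervals, but it could not make general pilot-study guidance into evidence that 20 per arm settles a safety objective.

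The claim matters because safety is both a main objective and a condition for progression, and because the described evidence carries no measure of uncertainty. The participants are frail older adults who are being prompted to get up and move more often. If the trial ends with few events, or with similar counts in the two arms, the protocol as written allows the intervention to be called safe, and its own sample size section can be cited in support. A reader planning the definitive trial would then not see how large a harm the data still allow.

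**Working it through.** **Inputs from the protocol article.** 20 per arm after attrition; 30% attrition; 60 recruited; 1:1 allocation. The article gives no fall, admission or adverse event rate and defines no relevant harm, so every event count or rate below is an assumption.

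**The plan's own figure.** 40 / (1 − 0.30) = 57.1, so 58; the article states 60, which is consistent and splits into 30 per arm. The 40 comes from general guidance without inputs and cannot be recomputed.

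The article does not say which participants form the safety denominator, so each result is given for n = 20 and n = 30 per arm.

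**1. What zero events in an arm exclude.** The one-sided 95% upper bound solves (1 − p)^n = 0.05, so p = 1 − 0.05^(1/n). The two-sided exact limit uses 0.025.

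| n per arm | one-sided 95% bound | two-sided 95% limit |
|---|---|---|
| 20 | 1 − 0.05^(1/20) = 13.9% | 1 − 0.025^(1/20) = 16.8% |
| 30 | 1 − 0.05^(1/30) = 9.5% | 1 − 0.025^(1/30) = 11.6% |

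**2. Precision of one arm's proportion.** For an assumed 4/20 the exact 95% interval is 5.7% to 43.7%. For an assumed 6/30 it is 7.7% to 38.6%.

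**3. Equal counts in the two arms.** Suppose the same number fall in each arm, so that the raw frequencies show no difference. On the log scale, with x events among n in each arm, SE = √[2(1/x − 1/n)].

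- 4/20 in each arm: SE = √[2(0.250 − 0.050)] = 0.632; 95% interval exp(±1.96 × 0.632) = 0.29 to 3.45. The score method gives 0.30 to 3.30.
- 6/30 in each arm: SE = √[2(0.1667 − 0.0333)] = 0.516; 95% interval exp(±1.96 × 0.516) = 0.36 to 2.75. The score method gives 0.37 to 2.68.

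By either method a risk ratio of 2 lies inside the interval, even with all 60 participants.

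**4. Pain and fatigue.** The 95% half-width for a difference in means, in SD units, is t(0.975; 2n − 2) × √(2/n).

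- n = 20: 2.024 × √0.1 = 0.64 SD.
- n = 30: 2.002 × √0.0667 = 0.52 SD.

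Equal observed means would therefore still be compatible with a worsening of about half an SD.

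**5. How far raw counts alone discriminate.** The table gives the exact binomial probability that the intervention arm shows no raw excess when its risk is truly doubled.

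| Assumed risk, control to intervention | n = 20 | n = 30 |
|---|---|---|
| 2% to 4% | 57% | 49% |
| 10% to 20% | 25% | 18% |
| 20% to 40% | 11% | 6% |

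When there is no harm at all, the intervention arm still shows a raw excess in 39% (10% rate) to 42% (20% rate) of trials at n = 20. Raw counts without intervals can therefore mislead in both directions.

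The chance of seeing at least one event when the true rate in an arm is 5% is 1 − 0.95^20 = 0.64, or 1 − 0.95^30 = 0.79.

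**The case against.** Descriptive safety reporting is usual in a feasibility trial. Intervals and the choice of denominator are often left to an analysis plan, which is not shown here. The criterion opens a further trial and not adoption of the intervention, and unmet criteria lead to adaptation before a full trial. The Trial Steering Committee meets every 3 months, and adverse events are also recorded ad hoc. The protocol nowhere says that the absence of a visible excess will be read as proof of safety.

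All of this stands, and it limits the weight of the point. It does not remove the sufficiency claim, which is stated outright, or the fact that a safety judgement gates progression while the described evidence consists of frequencies and means.

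A reader might go further and infer that a relevant harm would more likely be missed than seen. The documents do not support that. They plan no significance test for safety, so low power of such a test does not describe this design, and they give no harm rate. On the raw counts that are planned, a doubling of a common event would show as an excess in most trials: at n = 20, in 75% for 10% to 20% and 89% for 20% to 40%. An event with a 5% rate would be seen at least once with probability 0.64 to 0.79. Failing to see any event is the likelier outcome only for true rates below 3.4% (n = 20) or 2.3% (n = 30). Up to 30 per arm are exposed, so figures for 20 alone would also overstate the case.

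**Conclusion.** The point holds as one about an unsupported claim and a safety conclusion without a measure of uncertainty. The statement that 20 per arm suffices for safety does not follow from the reason given for it. Zero events in an arm would leave true rates up to 13.9% (n = 20) or 9.5% (n = 30) not excluded at one-sided 95%. Equal fall counts, such as an assumed 6/30 in each arm, would leave a risk ratio of up to about 2.7 not excluded.

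The zero-event bounds depend only on the number per arm. The risk-ratio intervals depend on assumed counts, because the documents give none. The sample is adequate to describe safety; it cannot carry an unqualified verdict of safe. The importance is moderate, since the next step is another trial.

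**What to change.** **Sample size.** Limit the claim for safety to describing events, and say what the number delivers, for example: *zero events in an arm would exclude a true rate above 13.9% with 20 participants, or above 9.5% with 30 (one-sided 95%); smaller rates cannot be excluded.*

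**Data analysis.** Report per arm the number and proportion of participants with at least one fall, hospital admission or adverse event, with exact 95% confidence intervals. Add between-arm differences with 95% confidence intervals, including those for mean pain and mean fatigue. State the denominator.

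**Progression criteria.** Have the Trial Steering Committee judge safety with those limits in view, and word a favourable conclusion as: *no safety signal identified; harms up to the reported upper limit not excluded.*

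**Cost.** Wording in three sections and a few intervals on data already being collected. No extra participants or measurements are needed. The downside is a more guarded safety statement.
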